#### Health-related quality of life (HR-QoL)

The Short Form 36 version 2 (SF-36 v2) questionnaire will be used to measure health-related quality of life (HR-QoL) [60]. The SF-36 v2 questionnaire consists of 36 items that cover 8 domains of HR-QoL: Physical functioning, Role-Physical, Bodily pain, General health, Vitality, Social functioning, Role-Emotional and Mental health [60]. The SF-36 survey has been established as valid and reliable in both interview and survey formats, and shows high reliability (α = 0.77 to 0.92) in people aged 65 years and older [61,62]. The scores for the SF-36 were originally based on a 0 to 100 scale, with higher scores indicating a better quality of life. However, this study will report Australian norm-based scores according to previously published guidelines [63]. The use of norm-based weights gives each domain score a mean of 50 and a standard deviation (SD) of 10, allowing change in scores to be assessed on a comparable scale. Basing the weights on Australian data (from the 2004 South Australian Health Omnibus Survey) [63] helps to account for cultural differences between populations in the way in which health and QoL are viewed [63]. Summary measures of the physical and mental components of the survey will also be calculated based on a factor analysis of the 8 domains among participants in the 2004 South Australian Health Omnibus Survey, yielding two separate overall summary scores: the physical component summary (PCS) and the mental component summary (MCS) scores.

Participants will also be asked to complete the Assessment of Quality of Life - 6D scale (AQoL-6D) questionnaire, which is a 20-item self-report instrument that considers six dimensions of health, including independent living, relationships, mental health, coping, pain and senses [64].

#### Cognitive function

The CogState Brief Battery computerised test (http://cogstate.com/) will be used to assess cognitive function. More specific details about these tests have been described previously [65,66]. Briefly, the tests have been designed to be easily administered and repeatable without eliciting practice or learned effects, and have been shown to provide sensitive and valid measurement for a range of different cognitive functions [65,66]. The battery of five tests that will be used for this study include: Groton maze learning test (measure of executive function and spatial problem solving), the Detection task (psychomotor function and speed of processing), the Identification task (visual attention and choice reaction time), One Card Learning task (visual learning with a pattern separation model) and the One Back task (working memory/attention).

#### Falls efficacy

Falls efficacy will be measured using the 16-item Falls Efficacy Scale-International (FES-I) version questionnaire [67], which is a tool for measuring the level of concern about falling during social and physical activities indoors and outdoors on a 4-point Likert scale (1 = not at all concerned to 4 = very concerned).

### Additional measures

#### Anthropometry and body composition

Height will be measured with a standardised portable stadiometer to the nearest 0.1 cm. Body mass will be measured to the nearest 0.1 kg. Body composition will be assessed using a whole body bioelectrical impedance (BIA) segmental body composition scales (TANITA BC-418, Tanita, Tokyo, Japan). This is a single-frequency (50Hz) BIA device that uses 8 polar electrodes that can provide a measure of whole body and segmental (arms and legs) fat mass (FM) and fat-free mass (FFM). An algorithm incorporating impedance, age and height will be used to estimate percentage fat mass. To standardise the measurement of weight and body composition, participants will be instructed to refrain from eating a meal 1 to 2 hours prior to the testing and to ensure normal hydration status. Participants will be measured wearing light clothing, standing erect and barefoot on the analyser’s footpads.

#### Lifestyle and medical history

A lifestyle questionnaire will be used to obtain detailed information on the participant’s ethnic and education background, employment history/status, medical history, previous history of any falls and fractures, family history of osteoporosis, current medication and dietary supplement use, smoking status, weekly television viewing and sitting time, and sun exposure habits.

#### Diet

Dietary intake will be assessed at each testing assessment using the Dietary Questionnaire for Epidemiological Studies Version 2 (DQES v2), a modification of the Cancer Council Food Frequency Questionnaire (FFQ) [68]. The DQES v2 covers 5 main types of dietary intake: 1) cereal foods, sweets and snacks; 2) dairy products, meats and fish; 3) fruit, 4) vegetables and 5) alcoholic beverages, incorporating 80 items. The DQES v2 is designed to be self-administered to determine the usual eating habits of the participants over the past 12 months at baseline. Participants will be instructed to record how often they ate each food listed on average over each time period. All questionnaires will be checked by the researchers for completeness. The performance of the Cancer Council FFQ has been evaluated in studies comparing the results of the questionnaire with those from weighed food records showing good agreement between methods [69].

#### Habitual physical activity

Total leisure and recreational physical activity will be assessed using the Community Healthy Activities Model Programme for Seniors (CHAMPS) questionnaire. This questionnaire has been designed for use in older adults and has been shown to be reliable, valid and sensitive to the changes in physical activity behaviour [70]. At each assessment, participants will record their weekly frequency and duration of participation in a ‘typical week’ of the preceding 4 weeks. The results will be reported as estimated kilojoules per week spent in moderate- to high-intensity activities.

#### Exercise compliance

Compliance with the exercise programme will be assessed by attendance at the supervised exercise sessions and completion of personal exercise cards that will be completed by the participants and checked by the trainers after each session.

#### Adverse events

All adverse events will be self-reported by the participant at 3, 6, 12 and 18 months and assessed by the research staff for seriousness, expectedness and causality following the guidelines recommended by the National Institute for Ageing (NIA) (http://www.nia.nih.gov/research/dgcg/clinical-research-study-investigators-toolbox/adverse-events). For this study, an adverse event will be defined as any health-related unfavourable or unintended medical occurrence (sign, symptom, syndrome, illness) that develops or worsens during the period of observation in the trial. Adverse events will be closely monitored until a resolution or stabilisation is achieved, or until it has been shown that the study intervention is not the cause of the injury. Participants will be asked to contact the research staff immediately in the event of a serious adverse event. Any adverse event sustained during the exercise programme will be recorded by the trainers and immediately reported to the research staff. The chief investigator will be informed and shall determine the seriousness and causality in conjunction with any medical staff treating the event. A serious adverse event that is deemed related to or suspected to be related to the exercise intervention will be reported to the ethics committee.

#### Cost-effectiveness analysis (CEA)

The CEA will be used to determine the monetary treatment costs of implementing the exercise programme and cost of outcomes (for example, falls and their consequences). The results will provide an incremental cost per fall averted for the DT-FPT and ‘step down’ programme. The incremental cost-effectiveness ratio (ICER) is the ratio of the incremental difference in treatment cost to the cost-saving (fewer falls). The ICER will be used in future decision-making on the allocation of resources, which maximises the health effects for a given amount of resources. The following measures will be collected: 1) the costs of implementing the programme (for example, staff costs, training, vehicle costs, capital costs and consumables), and 2) costs of health services (for example, directly related to a fall including inpatient hospital admissions, emergency department presentations and other health and community service contact) derived from the monthly calendars. The results will be expressed as the incremental cost (dollars) per fall averted among those randomised to the DT-FPT and ‘step down’ programme versus usual care. Research-related costs will not be included in the CEA.

### Sample size

Based on previous research in Australia [71-73], we anticipate that approximately 45% of the usual care control group will experience a fall throughout the study. To detect a 40% reduction in the rate of falls (for example, from 45% to 27%) in the DT-FPT group, we estimate that we will require 118 participants per group (2-tailed, *P* < 0.05 and power of 0.8). This allows for a 15% loss to follow-up due to death or withdrawal from the study. To account for cluster randomisation, we will assume a conservative intra-cluster correlation coefficient of 0.01 [74], giving a design effect of 1.19, assuming approximately 15 to 20 participants are recruited per village. This gives a sample size of 140 per group (280 participants from approximately 15 villages). This sample size will also provide sufficient power (0.9, 2-tailed, *P* < 0.05) to detect significant and clinically meaningful differences in many of the secondary outcome measures. Previous research has shown that 6 months of high-velocity resistance training in older adults can result in a 50% increase in peak muscle power (SD 18%) [20]. This mode of training has also resulted in a reduction in chair rise time of approximately 11% (SD 12%) and stair climbing time of approximately 7% (SD 10%) [20,21]. For the usual care control group, we estimate a mean change of 0 (SD 10%). Thus, to achieve 90% power at *P* < 0.05 (2-tailed), we estimate that 46 participants per group would be required to demonstrate between group differences of this magnitude in these measures. We will also have sufficient numbers to detect the smallest clinically significant differences in other measures of function and the SF-36. Perera *et al*. [75] calculated that a small meaningful change (difference) in function is around 5% (0.05 m/s gait speed) and a substantial change is around 10% (0.10 m/s gait speed). Since we will recruit a cohort at increased risk of falling, we anticipate greater changes based on previous work in healthy community-dwelling older adults (gait speed +7%, chair rise +13%) [21]. We estimate that 32 to 42 participants per group will be needed for a statistical power of 0.9 (2-tailed, *P* < 0.05) to detect differences between the groups of 14 to 25% in gait speed and chair rising time. Using data from a pilot study on dual-task stepping exercise [45], we estimate that we will need 48 participants per group to detect a 20% difference (SD 25%) in dual-task cost at 90% power (2-tailed, *P* < 0.05). For the sub-scales of the SF-36, we anticipate a change of 10 points in the DT + FPT groups with a small age-related change (decrease) in the controls. In various patient groups a 5 to 10% change is regarded as the minimal important difference. We note that the effects of resistance training on SF-36 are mixed, but differences of 15 to 52 points for the various sub-scales have been reported [76].

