### Primary outcome measures

The primary outcome will be the number of falls over the 6-, 12-, and 18-month period. The initial comparison of falls outcome between the two groups will be analysed according to the number of falls per person year and the proportion sustaining one or more falls. Subsequent analyses will allow for the non-independence of multiple events for the same participants. Participants will record all falls ((F (fall) or N (no fall)) each day on a monthly falls and adverse events calendar, which will be returned monthly via postage-paid mail. Any participants who do not return the monthly falls calendar will be contacted by telephone by the research staff. When a fall is recorded, a research staff member will administer a standardised questionnaire via telephone to record more specific details of the fall location, cause, injury, treatment and the healthcare utilisation. The fall event data will be coded using the International Classification of Diseases, 10th edition (ICD-10).

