
### Statistical methods

Primary analyses will be conducted on an intention-to-treat basis using STATA statistical software release (STATA, College Station, TX, USA). Per protocol analysis will also be performed by including all participants who are at least 80% compliant to the exercise (as measured by the number of exercise sessions attended). Initially, descriptive statistics will be computed to compare the intervention and control groups on background variables and baseline measures. Imbalances on prognostic factors between the groups will be adjusted for during analyses. Calculation of QoL scores (SF-36 v2, AQol-6D) will utilise published ‘weightings’ most relevant to this population. Baseline measures and changes in outcome variables over the study period for each study arm will be presented as means (± SD) with 95% confidence intervals. The effect of the intervention on the primary outcome variables will be assessed using negative binomial regression, to account for the non-independence of multiple events for the same participants and to allow for over-dispersion [77]. To account for clustering, the negative binomial regression analysis will be carried out using the generalised linear mixed modelling approach, with observations clustered within retirement villages; village will be modelled as a random effect. Differences between the intervention and control groups on the secondary outcome measures will be examined using linear mixed models with assessment times clustered within individuals and individuals clustered within villages. Village and, where appropriate (as determined by the likelihood ratio tests) individuals, will be modelled as random effects. The secondary outcome variables will be checked for normality prior to analysis and transformed appropriately if necessary. For both primary and secondary outcomes, random effects will be computed utilising robust standard errors. For all outcomes, primary analyses will compare unadjusted differences between the study groups at each follow-up. Supplementary adjusted analyses, with adjustment for potential covariates (baseline values of relevant outcome, age, sex, use of medication, chronic conditions, falls history and other background variables that show imbalances between the intervention and control groups) will also be conducted.

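### The single 0.8 power figure rests on fallers over the full 18 months, yet the 6- and 12-month comparisons are equally primary and, under simple assumptions, have much lower power

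*Protocol article*

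**What the plan says.** The Sample size section of the protocol article starts from a control risk over the whole study: "we anticipate that approximately 45% of the usual care control group will experience a fall throughout the study". The target is "To detect a 40% reduction in the rate of falls (for example, from 45% to 27%) in the DT-FPT group", for which the authors say "we will require 118 participants per group (2-tailed, *P* < 0.05 and power of 0.8"). They add: "This allows for a 15% loss to follow-up due to death or withdrawal from the study". Clustering enters through an intra-cluster correlation of 0.01, "giving a design effect of 1.19, assuming approximately 15 to 20 participants are recruited per village". The result is "This gives a sample size of 140 per group (280 participants from approximately 15 villages"). The Study design section fixes the study length at 18 months.

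Under Primary outcome measures: "The primary outcome will be the number of falls over the 6-, 12-, and 18-month period". Under Statistical methods: "For all outcomes, primary analyses will compare unadjusted differences between the study groups at each follow-up". The primary model there is negative binomial regression with village as a random effect. No section names one of the three time points as the main one, and none gives a faller proportion or a power figure for 6 or 12 months.

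**The concern.** One power figure stands beside three primary comparisons of equal standing, and its input can describe only the longest. The proportion who have fallen at least once cannot decrease with time. If 45% is the 18-month figure, fewer controls will normally have fallen by 6 and 12 months, and the same relative reduction then gives a smaller absolute difference.

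The 6-month comparison is the only one that covers the supervised programme alone. If its power is well below 0.8, a programme that works as assumed could easily fail to reach significance there, on an outcome labelled primary. This is a matter of missed effects, separate from the false-positive question that three primary tests raise. Any multiplicity adjustment would lower the power further.

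**Working it through.** **Inputs from the Sample size section.** Control 45%, intervention 27%, two-sided 5%, power 0.8, 15% loss, design effect 1.19, 140 per group.

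**The plan's own figures.**
- 1 + (20 − 1) × 0.01 = 1.19, so the design effect corresponds to 20 per village. 118 × 1.19 = 140.4, which reproduces 140.
- The 118 does not reproduce. The two-proportion formula with pooled null variance gives 111 per group for 45% v 27% before loss (122 with continuity correction). Allowing for 15% loss, 111 / 0.85 = 131 (or 144 with the correction).

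**Effective size per group.** No loss: 140 / 1.19 = 117.6. With 15% loss: 140 × 0.85 / 1.19 = 100.

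**Faller comparison.** Power = Φ{ [ |p1 − p2| − 1.96 √(2p̄(1 − p̄)/n) ] / √([p1(1 − p1) + p2(1 − p2)]/n) }.

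Two assumptions are added here that the plan does not state. The control hazard is constant, so control risk at t months is 1 − 0.55^(t/18). The intervention proportion is 0.6 times the control proportion at each time.

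| Time | Control v intervention | Power, n = 100 (15% loss) | Power, n = 117.6 (no loss) |
|---|---|---|---|
| 6 months | 18.1% v 10.8% | 30.5% | 35.0% |
| 12 months | 32.9% v 19.7% | 56.1% | 63.1% |
| 18 months | 45% v 27% | 75.9% | 82.5% |

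Example, 6 months, n = 100: difference 0.0723; 1.96 × 0.0497 = 0.0975; denominator 0.0495; (0.0723 − 0.0975) / 0.0495 ≈ −0.51; Φ = 0.305.

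Before loss and clustering, 80% power would need about 371 per group at 6 months and 175 at 12, against 111 at 18.

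Constant hazard has some support in the article. The Background says that at least one third fall each year, and 1 − (2/3)^1.5 = 45.6% over 18 months.

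**Other accrual assumptions, same test** (15% loss to no loss):
- Fallers accrue linearly: 26 to 29% at 6 months, 51 to 58% at 12.
- Constant hazard in both arms, ending at 45% and 27%: 38 to 43%, 62 to 69%.
- Constant hazard ratio of 0.6: 27 to 31%, 45 to 52% (and 58 to 66% at 18 months).
- Strong between-person variation (dispersion 1 to 2), arms ending at 45% and 27%: 52 to 72%, 69 to 81%.

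**Front-loaded effect, as an extreme bound.** Keep the control hazard constant and assume no effect in months 13 to 18. The cumulative control hazard is −ln 0.55 = 0.598, or 0.199 per 6 months; the intervention arm must reach −ln 0.73 = 0.315. The hazard ratio in months 0 to 12 is then (0.315 − 0.199) / 0.399 = 0.29. Power becomes about 78 to 85% at 6 months and 97 to 99% at 12.

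**Planned model, approximated.** Rate ratio 0.6, 15% loss (n = 100 after the design effect), var(log RR) = [(1/μ + k) + (1/(0.6μ) + k)] / 100, where μ is the mean control falls in the window. The 18-month mean is assumed to lie between 0.6 and 1.5, and k solves (1 + k·μ18)^(−1/k) = 0.55 so that 45% fall. Power is 29 to 34% at 6 months, 43 to 51% at 12 and 48 to 68% at 18.

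**The case against.** The strongest reply is that the documents give no 6- or 12-month faller proportion, so the plan's inputs alone yield no power figure there. That is right. The headline ranges rest on two added assumptions, and their width reflects loss to follow-up only.

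The constant-effect assumption also sits uneasily with the protocol's own premise. The Background and the section on the step-down programme say that benefits are largely lost once programmes end, which makes a larger early effect plausible. The bound above shows how far this could raise 6-month power. It is extreme, since it needs a hazard ratio of 0.29 for a year, but a milder form cannot be excluded. Applying the full 15% loss at 6 months is pessimistic too, because that figure covers the whole study.

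A reader might infer that the article promises 80% power at 6 and 12 months. It does not; it states 0.8 without saying which time point it covers. A reader might also infer that a non-significant 6-month result would be reported as a failed programme. Nothing in the article says so. Nor does the comparison imply that 0.8 is secure at 18 months: the stated loss alone brings it to about 0.76, and under the planned model much of the shortfall has nothing to do with the time point.

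A fuller protocol or analysis plan may rank the time points. But the article itself fixes both the sizing basis and three unranked primary comparisons, and these two statements do not fit each other. The choice of main time point remains a design decision for the investigators.

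**Conclusion.** The point holds as a mismatch between the sizing basis and the primary comparisons. The power calculation describes the 18-month faller proportion and cannot be carried over to the two shorter windows.

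With constant control hazard and the same 40% reduction throughout, power is about 31 to 35% at 6 months, 56 to 63% at 12 and 76 to 82% at 18. The other simple accrual assumptions widen the first two to about 26 to 43% and 45 to 69%. Strong between-person variation or an effect concentrated in the supervised phase would raise them, to 80% or above only in extreme cases. The negative binomial approximation, which depends on assumed mean fall counts, gives about 29 to 34%, 43 to 51% and 48 to 68%.

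The stronger reading, that the plan's own inputs establish a definite low power at 6 and 12 months, is not supported. The size of the shortfall depends on how falls accrue and when the effect occurs, and the article specifies neither.

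**What to change.** In the Sample size section, state that the calculation refers to the proportion of fallers over 18 months. Correct its power for the stated 15% loss (about 0.76 with 140 per group). Give expected power at 6 and 12 months, with the assumptions and the range they produce. The 18-month power under the planned negative binomial model belongs there too, so that 0.8 is not left unqualified.

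Under Primary outcome measures and Statistical methods, name the cumulative 18-month comparison, on which the trial is sized, as the primary one. Report 6 and 12 months as secondary estimates with confidence intervals, and do not read non-significance there as absence of effect. If the investigators prefer another main time point, they should name it and restate the power for it.

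This changes wording only and needs no extra participants or data. The cost is that the 6- and 12-month results lose primary status and the stated power looks less favourable.

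### The 118 per group cannot hold the stated 15% loss allowance; on the plan's own inputs 280 participants give about 76 to 77% power, not 80%

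*Protocol article*

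**What the plan says.** All the relevant text is in the Sample size section of the protocol article. The control assumption is that "approximately 45% of the usual care control group will experience a fall throughout the study". The target is stated as "To detect a 40% reduction in the rate of falls (for example, from 45% to 27%) in the DT-FPT group". From these the authors write "we estimate that we will require 118 participants per group", two-tailed, with P "< 0.05 and power of 0.8". The next sentence says of the 118: "This allows for a 15% loss to follow-up due to death or withdrawal from the study".

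Clustering comes afterwards: "we will assume a conservative intra-cluster correlation coefficient of 0.01", with a design effect of 1.19 for villages of roughly 15 to 20 participants. The conclusion is "This gives a sample size of 140 per group (280 participants from approximately 15 villages".

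**The concern.** The order of the steps matters. Loss is said to be inside the 118 already, and clustering is then applied on top. If the 118 does not hold a 15% allowance, nothing later in the calculation supplies one.

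This paragraph is the only power justification given for the primary outcome, and the error is in the favourable direction. Over 18 months in people aged 65 and over, attrition is a realistic threat, and the text tells the reader that it has been provided for. A null result would be judged against an 80% power figure that the stated assumptions do not produce.

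**Working it through.** **Inputs (all from the Sample size section).** p1 = 0.45, p2 = 0.27, difference 0.18, mean 0.36; two-sided alpha 0.05 (z = 1.960); power 0.80 (z = 0.8416); loss 15%; design effect 1.19; 140 per group.

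**Step 1: reproduce 140.** 118 × 1.19 = 140.4. The 1.19 is 1 + (20 − 1) × 0.01. The move from 118 to 140 is entirely the design effect, so any loss allowance must sit inside the 118.

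**Step 2: evaluable number per group, no loss.**
- z test, unpooled: (1.960 + 0.8416)² × (0.45×0.55 + 0.27×0.73) / 0.18² = 107.7
- Arcsine: 2 × (1.960 + 0.8416)² / 0.3778² = 110.0
- z test, pooled: [1.960 × √(2×0.36×0.64) + 0.8416 × √(0.45×0.55 + 0.27×0.73)]² / 0.18² = 110.4
- Log relative risk: (1.960 + 0.8416)² × (0.55/0.45 + 0.73/0.27) / [ln(0.27/0.45)]² = 118.1
- Pooled z with continuity correction: (110.4/4) × [1 + √(1 + 4/(110.4×0.18))]² = 121.3

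**Step 3: add the stated 15% loss (divide by 0.85) and compare with 118.**

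| Method | No loss | With 15% loss | Loss that 118 could absorb |
|---|---|---|---|
| Unpooled z | 107.7 | 126.7 | 8.7% |
| Arcsine | 110.0 | 129.4 | 6.8% |
| Pooled z | 110.4 | 129.9 | 6.4% |
| Log relative risk | 118.1 | 138.9 | none |
| Continuity-corrected | 121.3 | 142.7 | none |

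The last column is 1 − n/118. Inflating by 1.15 instead of dividing by 0.85 does not rescue the figure: the smallest result is 107.7 × 1.15 = 123.9. The nearest match found is a one-sided continuity-corrected test (98/0.85 = 115.3, so 116), which contradicts the stated two-tailed test.

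**Step 4: power of the planned 280.**
- Evaluable per group after loss: 140 × 0.85 = 119.
- Effective per group: 119 / 1.19 = 100.
- Pooled z: Φ[(0.18 × √100 − 1.960 × 0.6788) / 0.6668] = Φ(0.704) = 75.9%
- Unpooled z: Φ[0.18 × √100 / 0.6668 − 1.960] = Φ(0.740) = 77.0%
- Arcsine: 76.2%
- Less favourable methods: log relative risk 73.2%, continuity-corrected 71.0%

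**Step 5: sensitivity to village size.** Losing 15% also shrinks the villages, which lowers the design effect.
- 20 recruited, 17 retained: design effect 1.16, effective 119/1.16 = 102.6, power 77.0% (pooled) to 78.1% (unpooled).
- 15 recruited, 12.75 retained: design effect 1.1175, effective 106.5, power 78.5% to 79.6%.

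**Step 6: with no loss at all.** 140/1.19 = 117.6 effective per group gives 82.5% (pooled). By the z test the 80% is met if loss is small, but not at the 15% the plan itself assumes.

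**The case against.** The strongest reply is that 76% treats everyone lost as contributing nothing. Falls are recorded daily on calendars returned monthly, with telephone contact for non-returners (Primary outcome measures). The primary model is a negative binomial regression (Statistical methods). The missing-data paragraph plans to seek endpoint measures from withdrawals and to use multiple imputation. Someone who leaves at month 12 can still supply 12 months of data. As an illustrative assumption, if the 15% leave evenly over follow-up, about 7.5% of person-time is lost. Then 140 × 0.925 / 1.19 = 108.8 effective per group, with 79.4% (pooled) to 80.4% (unpooled) power as a rough proxy.

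This stands as a comment on the power the trial may achieve. It does not repair the printed calculation, which compares proportions and itself counts 15% as lost. Nor is this a matter of condensation in an article: every input and result is printed, and they do not agree.

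Three stronger readings are tempting and not supported.
- A reader might infer that 118 contains no allowance at all. By the z and arcsine tests it leaves room for about 6 to 9%; only by the log relative risk or the continuity-corrected test is there none.
- A reader might infer that 118 simply is the evaluable number before loss. It coincides with the log relative risk figure, but the article names no formula, so its origin cannot be assigned.
- A reader might apply a t reference for about 15 villages (13 degrees of freedom), which takes power to about 70%. The article specifies no such reference. That is a separate question of method and does not belong in a correction of the loss statement.

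**Conclusion.** The statement that 118 per group gives 80% power and already covers a 15% loss is wrong under every standard two-sided method tried. On the plan's own loss and design effect, 280 participants give about 76 to 77% power by the z or arcsine test. Recomputing the design effect for the smaller villages after loss gives about 77 to 80%. The shortfall is therefore at most about 4 points on those tests.

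The result assumes 45% versus 27%, participants lost contributing no information, and an intra-cluster correlation of 0.01, all as the paragraph has it. The gap is modest and changes neither the design nor the analysis, so this should be fixed but does not threaten the trial.

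**What to change.** Revise the Sample size paragraph in three ways:
1. Name the test and formula that produced 118.
2. Remove the statement that 118 allows for a 15% loss.
3. State that 280 recruited, with 15% loss and a design effect of 1.19, gives about 76 to 77% power for 45% versus 27%. If the authors prefer to recompute the design effect on village sizes after loss, they should give that figure and say so.

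The cost is wording only, with a less favourable power figure. Recruitment need not change. For information, keeping 80% under the plan's own loss and design effect would take 110.4 / 0.85 × 1.19 = 154.6, about 155 per group, by the pooled z test.
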